### Sample size

The overall sample size of the trial is powered for the phase III primary endpoint of PFS. An internal literature review investigating patients who have received up to three lines of previous therapy of any type and who responded to their most recent therapy with at least a PR suggested that 3 years is a reasonable estimate for median PFS in the control population (i.e., no consolidation), which translates to approximately 2 years from the time the participants are randomised (because it will be 3–24 months after previous therapy). An important clinical improvement would be an increase in median PFS from 2 to 3.3 years, a relatively large improvement, because consolidation is given at a time when patients would otherwise be in remission and treatment-free. The trial is powered to test the null hypothesis of no difference in PFS between the treatment arms, with a two-sided 5% level of significance and 80% power. Assuming 3 years of recruitment, 3 years of follow-up and allowing for a 5% drop-out rate, 188 participants are required (94 per arm) in order to observe 120 progression/death events. Losses to follow-up for the primary endpoint are expected to be extremely uncommon due to the short treatment duration and straightforward and regular follow-up schedule. A formal interim analysis on PFS will be carried out and reported to the data monitoring and ethics committee (DMEC) when half the required number of events have been observed (60 events).

The O’Brien and Fleming alpha-spending function [11] will be used to adjust for multiple testing to conserve the overall type I error, which recommends that the interim results be compared with a *p* value of 0.005, and the final analysis results are then compared with a *p* value of 0.047.

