### Randomisation

Following confirmation of eligibility and informed consent, MRD-positive participants will be randomised into the trial by an authorised staff member at the trial research site. Randomisation will be performed centrally using the Leeds Clinical Trials Research Unit (CTRU) automated 24-hour telephone registration and randomisation system. Participants will be randomised on a 1:1 basis to receive either obinutuzumab consolidation or no treatment. Participants will be informed of their treatment allocation in this open study.

A computer-generated minimisation program that incorporates a random element will be used to ensure treatment groups are well-balanced for the following participant characteristics: bone marrow MRD level at entry (≤0.3%, >0.3%), number of lines of previous therapy (one, more than one), age group (≤65, >65 years), sex (male, female), Binet stage of disease prior to most recent CLL therapy (A progressive or B, C) and previous rituximab (yes, no).

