### Secondary endpoint analyses

All secondary endpoint analyses comparing randomised participants will be assessed at the same time as the primary endpoint of PFS. The proportion of participants with undetectable MRD will be summarised (with 95% CIs) for participants randomised to consolidation therapy with obinutuzumab at 6 months post-randomisation and then at every time point at which MRD is assessed. CR, CRi and overall response (at least a PR) will be summarised (with 95% CIs) for participants randomised to consolidation therapy with obinutuzumab at 6 months post-randomisation and then at every time point at which response is assessed.

OS and treatment-free survival (TFS) (i.e., time from randomisation to next treatment or death) will both be assessed using Cox proportional hazards models to compare trials arms, adjusting for the minimisation factors. Kaplan-Meier curves, 95% CIs and median survival estimates will also be produced for both analyses by trial arm.

Participants who are registered and eligible but MRD-negative and so not randomised will also be followed for progression and death and will contribute to three secondary endpoint analyses. PFS, OS and duration of MRD negativity (i.e., time from end of most recent therapy for CLL to date of progression or death; date of death; or date of MRD relapse or death, respectively) will be assessed using Cox proportional hazards models to compare those who are MRD-negative at registration with those who become MRD-negative following consolidation therapy with obinutuzumab.

Occurrence and frequency of SUSARs, SARs, SAEs, AEoSI, AEs and treatment-related deaths will be summarised by trial arm and overall. In addition, all events will be summarised by maximum CTCAE grade reported and seriousness criteria, and all serious events will be summarised by Medical Dictionary for Regulatory Activities (MedDRA) System Organ Class, by trial arm and overall.

Mean QoL scores and 95% CIs, adjusted for the baseline score, will be calculated for all domains of the European Organisation for Research and Treatment of Cancer (EORTC) Core Quality of Life Questionnaire (QLQ-C30) and the CLL-specific module (EORTC QLQ-CLL16) for each trial arm and at each assessment time point and overall. Wilcoxon’s rank-sum tests will be used to compare the change in score for the trial arms from baseline to each time point.

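### The only between-arm quality-of-life test omits the baseline adjustment used for the reported means, which costs precision in a secondary endpoint with no stated power

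*Protocol article*

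**What the plan says.** The QoL paragraph of the protocol article (Secondary endpoint analyses) fixes two things.

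- **Estimate.** "Mean QoL scores and 95% CIs, adjusted for the baseline score, will be calculated for all domains" of the EORTC QLQ-C30 and QLQ-CLL16, and these are given "for each trial arm and at each assessment time point and overall".
- **Test.** The arms are compared with Wilcoxon's test: "rank-sum tests will be used to compare the change in score for the trial arms from baseline to each time point". No covariate is mentioned for it.

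No between-arm difference in adjusted means is described, and no p-value is tied to those means. In the same section, overall survival and treatment-free survival are handled differently, with "Cox proportional hazards models to compare trials arms, adjusting for the minimisation factors", so that for those endpoints one adjusted model supplies the comparison.

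Trial objectives lists QoL as a secondary objective. No target difference, standard deviation or power is stated for it.

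**The concern.** The baseline score is judged useful enough to adjust the reported means but plays no such part in the test. Subtracting baseline is not the same as adjusting for it. A change score fixes the baseline coefficient at 1, whereas regression estimates it, and with equal variances the best value is the correlation r. When r is below 1, the change score carries baseline noise that the adjusted analysis removes.

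Two consequences follow. The test needs a larger true difference to detect it, and a reader will see adjusted means and a p-value side by side that come from different analyses and may point different ways. This matters because consolidation is given to patients who, as Sample size notes, would otherwise be off treatment, so a QoL decrement during or soon after treatment is a result that readers will look for.

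The article names the test, so this is a choice it has made and not a detail left to the analysis plan.

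**Working it through.** **Plan's own figure.** There is none to reproduce, since no QoL calculation is stated.

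**Inputs from the document.** 94 participants per arm and 1:1 allocation (Sample size; Randomisation). The two-sided 5% level is stated for progression-free survival and is borrowed here for illustration.

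**Assumptions not in the document.** Baseline to follow-up correlation r of 0.3, 0.5 and 0.7. For the power figures, also a true difference of 0.4 SD and complete questionnaires.

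**Step 1: variance.** Let the SD be s at both times. Per participant:

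- change score: s² + s² − 2rs² = 2s²(1 − r)
- baseline-adjusted (ANCOVA): s²(1 − r²) = s²(1 − r)(1 + r)
- ratio: 2(1 − r) / [(1 − r)(1 + r)] = 2/(1 + r)
- information lost: 1 − (1 + r)/2

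For normal data the rank-sum test multiplies the ratio by a further π/3 = 1.047.

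| r | Ratio 2/(1+r) | Information lost | Ratio × π/3 |
|---|---|---|---|
| 0.3 | 2/1.3 = 1.54 | 35% | 1.61 |
| 0.5 | 2/1.5 = 1.33 | 25% | 1.40 |
| 0.7 | 2/1.7 = 1.18 | 15% | 1.23 |

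The direction does not depend on equal variances. With SDs s₀ at baseline and s₁ at follow-up, the change-score variance minus the adjusted variance is (s₀² + s₁² − 2rs₀s₁) − s₁²(1 − r²) = (s₀ − rs₁)², which is never negative. Only the size changes.

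**Step 2: power by formula**, 94 per arm, 0.4 SD, rank-sum on change against ANCOVA: 62% against 82% (r = 0.3), 76% against 89% (r = 0.5), 93% against 97% (r = 0.7).

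**Step 3: does this survive bounded or coarse scores?** Simulation with 4,000 trials per setting, 94 per arm and a shift of 0.4 SD on the underlying scale. Power is shown as rank-sum on change / ANCOVA / rank ANCOVA:

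| Score type | r = 0.3 | r = 0.5 | r = 0.7 |
|---|---|---|---|
| Normal | 61 / 81 / 79% | 75 / 88 / 86% | 93 / 97 / 95% |
| 0–100 with ceiling | 59 / 78 / 77% | 73 / 84 / 84% | 89 / 94 / 93% |
| Four-level item | 51 / 70 / 69% | 63 / 76 / 75% | 78 / 84 / 83% |

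With no true effect, the rank-sum test rejected in 4.3% to 5.5% of simulated trials and ANCOVA in 4.6% to 5.2%. Both are valid.

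**Step 4: agreement.** With normal scores, r = 0.5 and a 0.4 SD effect, rank-sum on change and ANCOVA reached different conclusions at the 5% level in about 15% of simulated trials.

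**The case against.** The strongest defence is that nothing here is invalid. Under randomisation a rank-sum test on change is unbiased and holds its error rate, as Step 3 shows. The paragraph can be read as two complementary displays: baseline-adjusted description by arm, and a distribution-free comparison suited to bounded, skewed scales. Baseline information is lost only from the test, since the adjusted means with intervals are already planned. QoL is secondary and has no power target. The size of the loss depends on a correlation that nobody has stated. It shrinks when r is high, and very heavy-tailed changes could favour ranks.

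Most of this stands and sets the limits of the point. What does not stand is skewness as a reason to leave baseline out. In the ceiling and four-level settings the loss persisted, and rank ANCOVA recovered nearly all of it. Skewness can justify ranks, but not an unadjusted comparison.

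Some stronger readings are tempting and are not supported:

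- A reader might infer bias from baseline imbalance. Under randomisation that imbalance is due to chance and averages to zero.
- A reader might infer that the p-value contradicts a planned adjusted difference. The article plans adjusted means by arm and no adjusted contrast, so the two may disagree but no stated contrast is contradicted.
- A reader might take QoL as the main measure of what consolidation costs patients. The article does not say so. Safety is a phase II primary objective, and toxicity is a separate secondary one.
- A reader might blame the visit-by-visit testing for ignoring correlation between visits. For a contrast at a single visit with complete data, joint modelling adds little beyond the baseline adjustment, and no figure for missing questionnaires is available to show more.

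**Conclusion.** The point holds as one of efficiency and coherence. The named QoL test leaves out the baseline adjustment that the article already applies to the means. Under equal variances this inflates the variance of the comparison by a factor of 1.54, 1.33 or 1.18 for assumed correlations of 0.3, 0.5 or 0.7, which is 35%, 25% or 15% of the information. The power figures also rest on an assumed 0.4 SD effect and full data on the planned 94 per arm. They illustrate the loss and do not forecast this trial, whose recruitment the article describes as difficult and which closed after two years against three assumed. The analysis as written is usable and unbiased. The change is a worthwhile improvement to a secondary endpoint and not a necessary correction.

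**What to change.** Make the main QoL comparison at each time point the baseline-adjusted difference between arms, with its 95% CI and p-value. It can come from an ANCOVA at that time point or from a repeated-measures model with the baseline score as covariate. The article names no model for the adjusted means, so the analysis plan should state one and draw both the means and the between-arm difference from it. Keep a rank-based ANCOVA or the Wilcoxon test on change as a sensitivity analysis for skewed or few-level domains.

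The cost is wording only. QoL questionnaires are already part of Baseline assessments, adjustment for the baseline score is already planned, and Statistical methods and analysis says that the analysis plan will be signed off before any analysis. No new data, visits or participants are needed.

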### Interim reports

An independent DMEC will review the safety and ethics of the trial while participants are receiving trial treatment, reviewing unblinded safety updates at 3-monthly intervals, and more detailed unblinded reports at yearly intervals. The phase II analyses on the proportion of participants with undetectable MRD will be reviewed by the DMEC when 9 and 23 participants have received at least 4 weeks of consolidation therapy with obinutuzumab and been followed until 6 months post-randomisation.

A formal interim analysis on the phase III primary endpoint of PFS will be reviewed by the DMEC when half the required number of events have been observed (60 events). The DMEC, in light of the interim data, and of any advice or evidence they wish to request, will advise the trial steering committee (TSC) if there are any concerns or reasons that the trial should not continue or if they believe that the trial results should be shared further.

### Sub-studies

Trial participants will also be invited to take part in the UK CLL Trials Biobank at the University of Liverpool. Participants will be approached at baseline with a separate consent form (research ethics committee reference 14/NW/1014), and biological samples will be sent to the University of Liverpool.

### Trial organisation and administration

The trial was developed by the GALACTIC Trial Management Group (TMG) with the support of the UKCLL/NCRI CLL Clinical Trials Sub-Group. The trial is funded by Cancer Research UK and Roche. The trial is sponsored by the University of Leeds (R&D Office, [name]), co-ordinated by the CTRU, University of Leeds, and is registered with two trial databases (ISRCTN64035629, EudraCT 2014-000880-42). The trial will be conducted in accordance with the principles of GCP in clinical trials, as applicable under U.K. regulations, the NHS Research Governance Framework and through adherence to CTRU standard operating procedures. The CTRU/sponsor has systems in place to ensure that serious breaches of GCP or the trial protocol are identified and reported. Ethical approval has been obtained from the National Research Ethics Service Committee Yorkshire & Humber – Leeds East (reference 14/YH/1199). A sample of data will be assessed by on-site source data verification by the CTRU, and this is not independent from the sponsor. The University of Leeds will be liable for negligent harm caused by the design of the trial. No additional compensation for clinical negligence will be provided for trial participants over that which is available to NHS patients. Obinutuzumab was provided by the sponsor only for the duration of protocol treatment, and subsequent treatment will be provided as per standard care.

A core project team, a TMG, a TSC and a DMEC have been established. The independent DMEC will review the safety and ethics of the trial, as overseen by the independent TSC. The TSC will monitor trial progress and the overall direction. Three-monthly interim safety reports are presented to the DMEC, with a full review done annually. The DMEC will also review SARs and SUSARs that result in death in real time. This committee, in light of the interim data and of any advice or evidence they wish to request, will advise the TSC if there are any concerns or reasons that the trial should not continue. The results of the study will be published in peer-reviewed publications and will be presented at relevant national and international conferences. There are no plans to use professional writers for presenting the outcomes of this trial. Any protocol changes are disseminated by the CTRU to the relevant parties. A SPIRIT checklist was prepared for this article (Additional file 1). A SPIRIT diagram was prepared for this article (Figs. 2 and 3).

## Discussion

Recruitment for the GALACTIC trial has been challenging. Recruitment numbers provided during feasibility assessment were significantly higher than observed during trial recruitment. We believe this was due partly to improved first- and second-line treatments providing a more durable remission, resulting in fewer MRD-positive patients at 3–24 months post-treatment. With more recent targeted therapies, treatment now continues for much longer than the standard 6-month period (with FCR, for example). This is likely to have reduced the number of eligible patients.

Whilst acceptance of the trial by patients has been high, the prospect of returning to hospital for further treatment is seen as an additional burden for many, particularly those who would be required to travel a long way to their nearest hospital. Because the trial protocol represents an additional cost for the NHS Trust compared with standard treatment, it has been difficult to enrol centres into the study, despite wide support from investigators. The aim of the findings of the GALACTIC trial is to compare consolidation with obinutuzumab with no consolidation with respect to PFS in patients who have responded to previous therapy with a CR or good PR with low levels of MRD.

## Trial status

The trial opened to recruitment in February 2015 using protocol version 2.0 (registered 30 October 2014) and closed to recruitment in February 2017.

## Abbreviations

AE: Adverse event
AEoSI: Adverse events of special interest
AR: Adverse reaction
BM: Bone marrow
CLL: Chronic lymphocytic leukaemia
CR: Complete remission
CR(i): Complete remission with incomplete marrow recovery
CT: Computed tomography
CTCAE: Common Terminology Criteria for Adverse Events
CTRU: Leeds Clinical Trials Research Unit
DMEC: Data monitoring and ethics committee
EORTC: European Organisation for Research and Treatment of Cancer
FCR: Fludarabine, cyclophosphamide and rituximab
GALACTIC: GA101 (obinutuzumab) monocLonal Antibody as Consolidation Therapy In CLL
GCP: Good clinical practice
HMDS: Haematological Malignancy Diagnostic Service
IRR: Infusion-related reaction
ITT: Intention to treat
IV: Intravenous
MRD: Minimal residual disease
NCRI: National Cancer Research Institute
NHS: National Health Service
OS: Overall survival
PFS: Progression-free survival
PML: Progressive multifocal leukoencephalopathy
PR: Partial remission
QLQ-C30: Core Quality of Life Questionnaire
QoL: Quality of life
SAE: Serious adverse event
SAR: Serious adverse reaction
SPIRIT: Standard Protocol Items: Recommendations for Interventional Trials
SUSAR: Suspected unexpected serious adverse reaction
TMG: Trial management group
TSC: Trial steering committee
WHO: World Health Organisation
